#### Economic evaluation for patients

A critical aspect of an evaluation such as this is to include a measure of impact from an economic perspective particularly one that could be utilised by commissioners to make decisions regarding the relative economic impact of an intervention. The costs of the intervention will be calculated on an individual patient basis. Staff time input, mileage travelled to patient homes and consumables used in the delivery of the rapid response intervention will be obtained from the service’s activity logs and patient records. Resource utilisation will be converted to costs using nationally validated unit costs, for staff time [13], and information from local financial managers for expenditure on travel and consumable items. The overall service utilisation of all participants during the time they are in the study will be collected for all patients in both arms including: general practice and community resources, outpatient, inpatient stays, out of hours service, Marie Curie nurse visits, and social care packages. This information will be gathered from providers’ databases for the period that each patient is in the study, and converted to unit costs [13]. The extent to which the rapid response service substitutes for other forms of health and social care (both community-based and inpatient) will be assessed.

The difference between the mean cost of patients in the rapid response arm and patients receiving treatment as usual will be calculated and compared with the difference between groups in the primary effectiveness outcome (proportion dying in preferred place of death). If the hospice intervention results in significantly improved outcomes at lower cost, it becomes the service delivery option of choice. If the intervention achieves superior outcomes (significantly more patients dying in their preferred place), but at higher cost, the cost per percentage point gain in dying in the preferred place will be calculated.

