### Randomisation

The rapid response service will be rolled out sequentially in the three centres with six months between the start of provision in each site (Figure 1). A simple probabilistic randomisation method will be used to determine the order in which the three areas start the rapid response service. Once the intervention is introduced in an area, it will be available to all patients within the catchment area of that hospice, while usual services will continue to be offered in the control areas until the new service is rolled out in that area.

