#### Sample size

The primary outcome measure for the patient evaluation is death in the first recorded preferred place of death. In current 'usual' service provided by Pilgrims Hospices, approximately 29% of patients die in their preferred place of death. Increasing this figure to 60% will be equivalent to the gold standard framework for end of life care. In order to detect a difference of this magnitude, with alpha at 0.05 and 90% power, using a 2-sided test, requires data to be collected on 49 new patients per site per six month period. The design of the study involves 9 cells (Figure 1) so the total sample size is inflated to 441. This equates to 147 for each of the three sites and 147 for each six monthly period.

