#### Data analysis

The main hypothesis will be tested using logistic regression controlling for baseline values and cluster using robust standard errors. Achieving preferred place of death will be presented as odds ratios, for control and intervention periods with associated 95% confidence intervals. A secondary analysis will explore last stated preferred place of death versus actual place of death using a similar approach.

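### The cost effect is stated as a plain difference of arm means, although the staggered roll-out gives the two arms different mixes of centres and six-month periods

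*Protocol article*

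**What the plan says.** The Protocol article, Economic evaluation for patients, gives the estimator: "The difference between the mean cost of patients in the rapid response arm and patients receiving treatment as usual will be calculated". The result is then set against the between-group difference in the proportion of patients who die where they wished. A rule follows: "If the hospice intervention results in significantly improved outcomes at lower cost, it becomes the service delivery option of choice". If outcomes are better but cost is higher, a cost per percentage point gained is calculated instead. The section mentions no centre, period or baseline term.

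The design is under Randomisation: "The rapid response service will be rolled out sequentially in the three centres with six months between the start of provision in each site". Only the sequence is random: "A simple probabilistic randomisation method will be used to determine the order in which the three areas start the rapid response service". Each area moves one way, from control to intervention: "usual services will continue to be offered in the control areas until the new service is rolled out in that area". Under Patient evaluation, Sample size: "The design of the study involves 9 cells", with 49 patients in each, 147 per site and 147 per six-month period.

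The article does name adjustment for its other two quantitative analyses. Place of death is analysed by "logistic regression controlling for baseline values and cluster using robust standard errors", and carer outcomes are adjusted for baseline values and carer burden.

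**The concern.** In a one-way staggered roll-out, early-starting centres and late periods are over-represented among intervention patients, and late-starting centres and early periods among controls. A difference of arm means therefore mixes the service effect with cost differences between centres and with changes in cost over time. The article argues that the design guards against policy shifts during the study. A pooled difference of means gives that protection up.

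Cost saving is a stated secondary hypothesis, and the article says the economic result should be usable by commissioners. The sign of the cost difference selects the branch of the decision rule, and its size is the numerator of the cost per percentage point. The difference in proportions in that ratio, if also taken straight between groups, has the same defect.

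**Working it through.** **Inputs.** Three centres, starts six months apart, control until start (Randomisation). Nine cells of 49; planning rates 29% and 60%; two-sided 5% level; 90% power (Patient evaluation, Sample size). Centre and period costs are not given.

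**The plan's own layout figure.** Two proportions with unpooled variance:

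n = (0.29×0.71 + 0.60×0.40) × (1.960 + 1.282)² / 0.31² = 48.75, so 49 per cell. Then 9 × 49 = 441 and 3 × 49 = 147. The stated figures reproduce, which supports reading the layout as three centres by three periods with equal cells.

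**Arm composition.** Figure 1 is not shown, so two layouts were taken. Each entry is the share of an arm's patients, in order first/second/last centre or period 1/2/3.

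| Layout | Intervention, centres | Control, centres | Intervention, periods | Control, periods |
|---|---|---|---|---|
| First start in period 1 (294 v 147 patients) | 3/6, 2/6, 1/6 | 0, 1/3, 2/3 | 1/6, 2/6, 3/6 | 2/3, 1/3, 0 |
| First start in period 2 (147 v 294 patients) | 2/3, 1/3, 0 | 1/6, 2/6, 3/6 | 0, 1/3, 2/3 | 3/6, 2/6, 1/6 |

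**Weights in the difference of means** (intervention share minus control share). In both layouts these are +1/2, 0, −1/2 on the centres in starting order, and −1/2, 0, +1/2 on periods 1 to 3. Hence, with additive centre and period effects:

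difference of arm means = service effect + ½ (first centre − last centre) + ½ (period 3 − period 1).

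**Sensitivity to layout.** With a fourth, common baseline period (12 cells, so not the stated 9), the centre shares are 3/6, 2/6, 1/6 against 1/6, 2/6, 3/6. The centre weights become +1/3, 0, −1/3. The period weights are −1/2, −1/6, +1/6, +1/2.

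**Illustrations (assumed costs, true service effect zero, 3×3 layout).**
- Centre gap of 1,000 pounds, no time trend: ½ × 1,000 = 500 pounds. Gaps of 500 and 2,000 give 250 and 1,000.
- Adding a rise of 500 pounds per period: period 3 − period 1 = 1,000, so a further 500, giving 1,000 pounds in all for the 1,000-pound gap.
- Least squares with centre and period terms returns zero in each of these cases.

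**Role of the random order.** Over the six possible orders each pair of centres appears equally often as first and last in either direction, so the centre term averages to zero. The trial uses one order, and there the term is zero only if the first and last centres happen to have equal mean cost. The period term is the same under every order.

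**Price of adjustment.** Let v be the variance of one cell mean. In the 3×3 layout the unadjusted variance is (1/3 + 1/6)v = 0.5v. With centre terms, the within-centre variation in exposure is 2/3 + 2/3 + 0 = 4/3, giving 0.75v: ratio 1.5, standard error ×1.22. With centre and period terms, the residual variation is six cells of (1/3)² = 2/3, giving 1.5v: ratio 3, standard error ×1.73.

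**The case against.** The best reply is that the article never uses a word such as raw or unadjusted. An adjusted incremental cost is also a difference in mean cost, and a condensed article may leave covariates to a fuller document. This stands to the extent that a reader should not infer a commitment to no adjustment. But the sentence gives an estimator and attaches a service-choice rule to it, while adjustment is named for the other two analyses. Followed as written, it yields a confounded figure.

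Stronger readings are tempting and are not supported:
- **That the result is certainly biased by centre.** The order is randomised, so the centre part is chance imbalance in the realised order. Only the period part is systematic, and only if costs change over time.
- **That the first centre supplies most intervention patients and the last centre most controls.** The shares are 50% to 67%, and in each layout one of the two is exactly half.
- **That a cost test would have an inflated false-positive rate.** The economic section plans no test or interval for cost; its reference to significance attaches to outcomes only.
- **That the error is large.** The three centres belong to one organisation, each has a 16-bed ward, and staff time and service use are valued at national unit costs. This points towards modest price differences, though differences in use can remain.

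Adjustment is also not always more accurate. With 147 v 294 patients, the unadjusted variance is 1/147 + 1/294 = 0.0102 in squared patient-level SDs, and the fully adjusted variance is 3 × 0.0102 = 0.0306. If the first-to-last centre gap were 0.25 SD with no time trend (assumption), the unadjusted mean squared error would be 0.0102 + 0.125² = 0.0258, which is the smaller. At 0.5 SD it would be 0.0102 + 0.25² = 0.0727, which is the larger.

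**Conclusion.** The point holds in a limited form. The stated cost comparison does not fit the staggered design. In either 3×3 layout it carries half of any first-to-last centre cost gap and half of any last-to-first period cost gap; with an added common baseline period the centre share is one third. These weights rest on equal cells and additive centre and period effects, and on a layout inferred without Figure 1. More patients would not reduce the offset. Its size in pounds cannot be derived from the article, and the 500-pound figure is an illustration only. What makes it worth correcting is that time trends in cost and chance centre imbalance feed directly into the decision rule and the cost per percentage point.

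**What to change.** In Economic evaluation for patients, define the cost difference as the service coefficient from a patient-level regression on the cost scale, with terms for centre and six-month period. Take the percentage-point difference in achieving preferred place of death from a model with the same terms, expressed as a difference in proportions, not an odds ratio. Use these two adjusted differences in the decision rule and in the cost per percentage point. Report the unadjusted differences alongside.

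This takes a few lines of text and no new data, because centre and dates are already held. The cost is a wider interval, by the factors shown in the working. If centre and period differences prove small, the adjusted estimate may be the less accurate of the two, which is why both should be shown and the adjusted one named in advance as the basis for the rule.

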### Carer evaluation

Carers will be included in the study if they cared for a patient who died within the study period. Only one main carer per patient will be sampled.

#### Sample size

The primary outcome measure for the carer evaluation is quality of life, measured using SF12 [14], at patient intake to hospice services and 8 months later. A clinically important change for quality of life is estimated as a 5 point change on the SF12. This equates to a medium effect size difference between the groups of 0.5. In order to establish an effect size difference of this magnitude at 80% power, with alpha at 0.05 requires 56 people within each of the intervention and control cells of the study. Previous experience with similar populations suggests 50% will refuse consent and the follow up rate at 8 months will be of the order of 70%. This inflates the required sample of potential carers to 160 in each cell of the study design, a total of 1440. Assuming that 40% of end of life patients have no primary carer the numbers seen over the study period based on current referral rates allow for a potential recruitment population of 1800.

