#### Data collection

Data collection for the patient outcome will be conducted in a two stage process (Figure 2). First, patients will be entered onto a database after they have had their first assessment with a member of the hospice team. It is at this point that carers will be sent a questionnaire. Patient preferences will then be monitored while under hospice care in order to identify any changes in preferences over time. At the end of the study period, any patients still alive will be excluded as well as their carer. Patients who have died during the study period and who had a preferred place of death recorded in the hospice notes will be included. At this point, these patients’ preference data, place of death, diagnosis, demographic data and service utilisation data will be extracted from service records. Patients who died during the study period but did not have a preferred place of death recorded will be excluded from analysis, but carers of this group will be included.

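### The 56 carers per cell does not follow from its stated inputs, and neither 1,440 nor 1,800 allows for excluding carers of patients who survive the study

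*Protocol article*

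**What the plan says.** All references are to the protocol article.

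- Carer evaluation, Sample size, sets the outcome and its two time points, the second counted from intake: "The primary outcome measure for the carer evaluation is quality of life, measured using SF12 [14], at patient intake to hospice services and 8 months". The target is given as "A clinically important change for quality of life is estimated as a 5 point change on the SF12", and then "This equates to a medium effect size difference between the groups of 0.5".
- The same paragraph gives the number: "In order to establish an effect size difference of this magnitude at 80% power, with alpha at 0.05 requires 56 people". This applies to every cell, whether intervention or control. The paragraph states neither sidedness nor a baseline to follow-up correlation. It then allows for 50% refusal and 70% follow-up, reaching 160 per cell and 1,440 over the design.
- On feasibility, after assuming that 40% of patients have no primary carer, it says that "the numbers seen over the study period based on current referral rates allow for a potential recruitment population of 1800".
- Patient evaluation, Data collection, says: "At the end of the study period, any patients still alive will be excluded as well as their carer". The opening of Carer evaluation likewise limits inclusion to carers of patients who died in the study period.
- Carer evaluation, Data analysis, plans analysis of covariance adjusting for baseline values and carer burden, with clustering explored through robust standard errors.

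**The concern.** A sample size paragraph should let a reader recover its number from its inputs. Here the effect size, power and alpha are all given, and the result matches neither a two-sided nor a one-sided calculation. The later steps (160, then 1,440) are built on it.

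The feasibility statement is a second, separate gap. It compares 1,440 carers needed with 1,800 potential recruits, but the study keeps only carers whose patient dies before it ends. If a material share of patients survive, the margin between the two figures shrinks or disappears, most of all for patients referred late. At stake are the accuracy of the stated power for the carers' primary outcome and of the claim that enough carers exist.

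**Working it through.** **Inputs.** From Carer evaluation, Sample size: difference 5 points, effect size 0.5 (so SD 10), alpha 0.05, power 80%, 50% refusal, 70% follow-up, 40% without a carer. From Setting: about 2,000 referrals a year. From Randomisation and the patient Sample size: nine cells over three sites, hence three six-month periods, or 1.5 years. Two-sided testing is stated only for the patient calculation ("with alpha at 0.05 and 90% power, using a 2-sided test"), so both cases are tried for carers.

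**1. The 56.** Per compared cell, n = 2(z_alpha + z_power)² / d².

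- Two-sided: 2(1.960 + 0.842)² / 0.25 = 62.8, so 63. The t-test gives 63.8, so 64.
- One-sided: 2(1.645 + 0.842)² / 0.25 = 49.5, so 50. The t-test gives 50.2, so 51.

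Power with 56 per cell: 0.5 x √(56/2) = 2.646.

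- Two-sided: Φ(2.646 − 1.960) = 75.4%; t-test 74.6%.
- One-sided: Φ(2.646 − 1.645) = 84.2%; t-test 83.8%.

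The 56 is exactly the two-sided normal-approximation n for 75% power. With 56 per cell, the effect detectable at 80% power (two-sided) is 0.534.

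**2. What would make 56 right.** Analysis of covariance multiplies the variance by (1 − r²). Setting 62.8(1 − r²) = 56 gives r ≈ 0.33. Setting 63.8(1 − r²) = 56 gives r ≈ 0.35.

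**3. The inflation.** 56 / (0.5 x 0.7) = 160, and 160 x 9 = 1,440. Both reproduce, so the only discrepancy is in the 56. For comparison, 63 / 0.35 = 180 (1,620 in total) and 64 / 0.35 = 183 (1,647 in total).

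**4. The 1,800.** 2,000 x 1.5 x 0.60 = 1,800 exactly. This counts every referral with a carer, with nothing removed for survivors. The smallest death fraction that leaves 1,440 is 1,440 / 1,800 = 80%. The article gives no such fraction. Over an assumed range:

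| Share dying within the study | Eligible carers |
|---|---|
| 50% | 900 |
| 60% | 1,080 |
| 70% | 1,260 |
| 80% | 1,440 |
| 90% | 1,620 |

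**5. Where the loss falls (illustration only).** Assume exponential survival with mean m months, uniform entry and equal referrals across cells (1,800 / 9 = 200 per cell). The share dying by study end is 1 − (m/T)(1 − e^(−T/m)), with T = 6 for last-period entrants and T = 18 for the whole study.

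| Mean survival | Last-period cell, of 200 | Whole study, of 1,800 |
|---|---|---|
| 1.5 months | 151 | 1,650 |
| 3 months | 114 | 1,501 |
| 6 months | 74 | 1,230 |

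Last-period cells fall below 160 in all three rows. The whole-study pool falls below 1,440 only in the third; under this model it does so once mean survival exceeds about 3.6 months.

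**6. The pooled comparison.** Nine cells of 56 give 504 completers. Assuming a split of three cells against six (Figure 1 is not shown), that is 168 v 336, with power above 99% at effect size 0.5 if clustering is ignored. With design effect 1 + 55 x ICC, assumed ICCs of 0.01, 0.02 and 0.05 give design effects of 1.55, 2.10 and 3.75, and power of about 99%, 95% and 77%.

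**The case against.** The strongest defence of 56 is the planned analysis. It adjusts for baseline, a modest correlation would bring 56 to 80% power, and a journal article may leave that parameter to the full protocol. This stands in part. It means that 56 may be attainable, so calling it simply wrong would go too far. It does not make the printed statement reproducible, because the paragraph presents a plain between-group effect size and mentions no correlation.

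On the 1,800, the questionnaire goes out after the patient's first assessment and survivors' carers are dropped only at study end. At the time of approach, every carer is therefore a potential recruit, and the figure is fair as labelled. That also stands. The gap is then a missing loss factor between the carers approached and the carers analysed, and it remains whichever figure is adjusted.

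A reader might infer that the carer comparison is underpowered. The document does not support this: 56 is stated for each cell, not for each arm, and the pooled groups are several times larger. Whether they suffice depends on the ICC, which the calculation does not give.

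A reader might also infer that too few carers will be found. That too needs an assumed survival time, and two of the three illustrative values leave more than 1,440 overall.

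**Conclusion.** The point holds as a correction of stated figures. From the paragraph's own inputs, 56 per cell gives about 75% power two-sided and unadjusted, against the 80% claimed; 63 to 64 would be needed. One-sided testing does not reproduce it either. The 160 and 1,440 carry the discrepancy forward.

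The second part also holds. Neither 1,440 nor 1,800 allows for excluding carers of surviving patients, so the stated need is met only if at least 80% of referred patients with a carer die within the study, with last-period referrals hit hardest. That 1,800 counts all referrals is inferred from the exact arithmetic match and an 18-month study; the article does not say so.

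Neither part demonstrates lost power in the pooled comparison or an overall shortage of carers.

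**What to change.** In Carer evaluation, Sample size:

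- State the sidedness. Then either keep 56 and give the power as about 75% (detectable effect about 0.53 at 80% power), or state and justify the baseline to follow-up correlation, about 0.33 to 0.35, under which the planned analysis of covariance gives 80%.
- Add the expected fraction of patients dying within the study to the inflation, and restate the pool of eligible carers on that basis, noting the lower fraction in the last period.
- Give the power of the pooled intervention v control analysis of covariance, with an allowance for clustering and the ICC assumed.

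The cost is the rewording of one paragraph and a less favourable stated figure. No extra enrolment is proposed. Raising the per-cell number to 63 or 64 instead would mean approaching 1,620 to 1,647 carers, which is not free, and nothing here shows that it is needed.

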#### Outcomes for carers

Carer outcomes will be measured at baseline on patient intake and 8 months later using self completion postal questionnaires. The primary outcome measure will be the short-form SF12 [14]. Other outcomes include a measure of anxiety and depression (HADS) [15], a measure of health utility (EQ-5D) [16], and caregiving demand [17] measured at baseline only. In the follow-up questionnaire a satisfaction with care questionnaire will be included.

#### Data analysis

Prior to the analysis of outcomes distributional assumptions will be checked and the analytical framework adjusted to account for these. Analysis of quality of life will be conducted using analysis of covariance, or non-parametric equivalent, adjusting for baseline values and carer burden. Potential cluster effects will be explored using robust standard errors. A similar approach will be employed for other carer outcomes. Results will be presented as means per group and appropriate estimates of precision.

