**Figure 1 F1:**
[figure not shown]
Time of service delivery by area.

The evaluation design randomises centres and therefore does not require the blind randomisation of individual patients into intervention or control group which would create serious ethical and practical problems. It is a design that protects from a number of potential sources of bias: contamination between patients, changes in health policy over time and resentful demoralisation of patients [11]. The design simultaneously addresses the situational and resource factors that arise from implementing an intensive new service across a wide area.

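### The carer SF12 model adjusts for neither centre nor calendar period, although three centres start the service at staggered times, so service exposure is tied to both

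*Protocol article*

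**What the plan says.** The Randomisation section describes a staggered introduction: "The rapid response service will be rolled out sequentially in the three centres with six months between the start of provision in each site". Chance decides only the order: "A simple probabilistic randomisation method will be used to determine the order in which the three areas start the rapid response service". The text under Figure 1 confirms the unit of allocation: "The evaluation design randomises centres and therefore does not require the blind randomisation of individual patients".

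For carers, the Sample size section states: "The primary outcome measure for the carer evaluation is quality of life, measured using SF12 [14], at patient intake to hospice services and 8 months" after intake. The Data analysis section under Carer evaluation then gives the model: "Analysis of quality of life will be conducted using analysis of covariance, or non-parametric equivalent, adjusting for baseline values and carer burden". Clustering gets one further sentence: "Potential cluster effects will be explored using robust standard errors". Other carer outcomes are to be handled in a similar way.

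The patient analysis is worded more firmly: "logistic regression controlling for baseline values and cluster using robust standard errors". The article gives the carer model no centre term and no period term.

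**The concern.** Under staggered starts, the centre that begins first supplies more intervention carers and the centre that begins last supplies more control carers. Intervention carers also come disproportionately from later periods. A simple arm comparison therefore mixes the service effect with differences between centres and with change over time.

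Baseline SF12 removes differences already present at intake. It does not remove differences that arise afterwards, for example in local services or bereavement support. Robust standard errors alter the stated uncertainty but not the estimate. At stake is the hypothesis about carers' quality of life: a nominally significant result in either direction could reflect which centre was drawn to start first, or calendar drift.

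**Working it through.** **Inputs from the protocol.** Three centres and nine cells; 56 analysed carers per cell; a target of 5 points equal to an effect size of 0.5, hence SD = 5/0.5 = 10; 50% refusal; 70% follow-up.

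**The plan's own figures.** 56/(0.5 × 0.7) = 160 per cell and 160 × 9 = 1440, as stated. Analysed carers: 56 × 9 = 504. The 56 itself is not what the usual two-sided formula gives (2 × (1.96 + 0.84)²/0.5² = 63); that is a separate matter and does not affect this point.

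**Assumptions.** Figure 1 is not shown, so two layouts were tried: intervention periods by centre of 3/2/1 or 2/1/0. Baseline correlation is taken as 0.5, so residual variance = 100 × (1 − 0.25) = 75. The between-centre variance of follow-up SF12 given baseline is taken as 0.5, 1, 2 or 5 (SD about 0.7, 1.0, 1.4, 2.2 points).

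**Step 1: centre weights in the arm contrast (intervention minus control).**
- 3/2/1: (1/2, 1/3, 1/6) − (0, 1/3, 2/3) = (+0.5, 0, −0.5)
- 2/1/0: (2/3, 1/3, 0) − (1/6, 1/3, 1/2) = (+0.5, 0, −0.5)

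Centre means of +2/0/−2 points thus shift the estimate by 2.0 points; +1/0/−1 shifts it by 1.0.

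**Step 2: period weights (periods 1, 2, 3).**
- 3/2/1: (1/6, 1/3, 1/2) − (2/3, 1/3, 0) = (−0.5, 0, +0.5)
- 2/1/0: (0, 1/3, 2/3) − (1/2, 1/3, 1/6) = (−0.5, 0, +0.5)

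**Step 3: false-positive rate without a centre term, ordinary standard errors, no period effect.** The arms hold 336 and 168 carers (in one order or the other), so sampling variance = 75 × (1/336 + 1/168) = 0.67 and SE = 0.82. Centre variation adds (0.5² + 0.5²)τ² = 0.5τ². The rate is 2 × [1 − Φ(1.96 × 0.82/√(0.67 + 0.5τ²))].

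| Centre SD (points) | True variance | Rate by formula | Simulated |
|---|---|---|---|
| 0 | 0.67 | 5% | about 5% |
| 0.7 | 0.92 | 9% | 9% |
| 1.0 | 1.17 | 14% | 14% |
| 1.4 | 1.67 | 21% | 21–22% |
| 2.2 | 3.17 | 37% | 37% |

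**Step 4: robust standard errors.** In the same simulations (3000 runs per setting), cluster-robust errors on three centres rejected in 20–25% of runs with a normal reference, and in 4–8% with t on 2 degrees of freedom. Heteroscedasticity-robust errors behaved like ordinary ones.

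**Step 5: centre term only.** In the 3/2/1 layout the changing centres have exposure (0,1,1) and (0,0,1). Centred, these are (−2/3, 1/3, 1/3) and (−1/3, −1/3, 2/3), with total sum of squares 4/3. The period weights become (−0.75, 0, +0.75), and the same holds for 2/1/0. A 3-point drift from period 1 to period 3 would move this estimate by 2.25 points, against 1.5 without the centre term. SE = √(75/(56 × 4/3)) = 1.0. With an assumed period SD of 1 point, the added variance is 2 × 0.75² = 1.125 and the rate is 2 × [1 − Φ(1.96 × 1.0/√(1.0 + 1.125))] = about 18%. Simulated settings lay around this value, at 16–20%.

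**Step 6: centre and period.** Removing both row and column means from the exposure pattern leaves a sum of squares of 2/3. SE = √(75/(56 × 2/3)) = 1.42. Simulated false-positive rates were 4–6% in every setting, with or without period effects.

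**Step 7: power for 5 points with both terms.** 5/1.42 = 3.53, and Φ(3.53 − 1.96) = 94% (simulated 93–94%). If baseline explained nothing, SE = √(100/(56 × 2/3)) = 1.64, 5/1.64 = 3.05, and power = 86%.

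**The case against.** The strongest reply has five parts.

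- **Start order is randomised.** A reader might infer that the estimate is simply biased. It is not: averaged over possible orders, the centre weights cancel. What stands is narrower. With three centres, only one order is realised, the estimate is confounded with centre given that order, and the ordinary interval omits the resulting variance.
- **The protocol does mention robust standard errors.** A reader might take 9–37% as the error rate of the analysis as written. The text does not settle that. Those figures are for ordinary standard errors, and it is only an inference from the word explored that these would accompany the main result. Robust errors change the rates (Step 4), but the article states no small-cluster reference distribution, and the estimate stays the same.
- **A centre term might look sufficient.** It is not, for the reason in Step 5. The text under Figure 1 claims protection against policy change over time, and a purely within-centre comparison would weaken that protection.
- **Size is unknown.** No intraclass correlation is given, the centres belong to one organisation with like facilities, and baseline SF12 absorbs intake differences. The upper end of the range may not apply, and with no residual centre or period differences there is no inflation from ordinary standard errors.
- **Scope.** Carer quality of life is a secondary hypothesis, and an unseen analysis plan could add terms. But the article states the covariates outright. Its allowance for adjusting the analytical framework concerns distributional assumptions, not the design.

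**Conclusion.** The point holds in this form: the stated carer model leaves out both design factors to which exposure is tied. The arm contrast carries half of any residual first-to-last centre difference and half of any residual period 1 to period 3 change. At nominal 5%, the false-positive rate with ordinary standard errors is about 9% to 37% for assumed residual centre SDs of 0.7 to 2.2 points and no period effect. These figures rest on equal cells, the two assumed layouts, a baseline correlation of 0.5 and assumed centre differences; the documents supply none of the last two. The direction of the problem does not depend on those sizes.

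The documents do not show that the carer result would be wrong, nor that the patient primary analysis shares the fault, since that analysis names cluster. This is a worthwhile and inexpensive improvement to the carer evaluation.

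**What to change.** In the Data analysis section under Carer evaluation, define the carer primary model as an analysis of covariance of follow-up SF12 on arm, baseline SF12, carer burden, centre and six-month period, with centre and period as fixed effects (two indicators each). Use the same centre and period terms for HADS and EQ-5D. Report this model's estimate and interval as the main result, and replace the sentence on exploring cluster effects accordingly.

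Both terms are needed. The model assumes that centre differences are constant over time and that calendar changes are common to the centres; the text should say so.

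The cost is wording and precision. Centre and period are inherent in the design, so no new data are required. The standard error rises from about 0.82 to 1.4 points at the assumed baseline correlation. Power for 5 points with 504 analysed carers remains about 86–94%, against the 80% planned.
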